### Platform performance

AHCL system characteristics will be extracted from CareLink™ software and system settings, insulin delivery distribution (e.g., TDD, percentage insulin delivered through automation), system performance (e.g., alarm frequency, percentage time spent in SmartGuard™, sensor wear percentage time), and markers of therapy adherence (e.g., frequency of infusion set changes, bolus frequency) at the end of the RCT will be reported. Episodes of SmartGuard™ exits will be assessed.

### Qualitative study

It is important to understand participants’ lived experiences with AHCL technology. Semi-structured one-to-one interviews (in-person or via videoconference) will be conducted with 10 to 15 participants aged 13–25 years, and 10 to 15 guardians of participants aged 7–15 years using purposive sampling. Interviews will occur during the extension phase following the completion of the 13-week RCT, and interviewees will be interviewed after a minimum of one month of AHCL use. Interviews will last approximately 60 min and will be digitally recorded and transcribed verbatim for analysis in NVivo (Lumivero, Denver, CO). Thematic analysis will be performed to identify barriers and facilitators of AHCL use.

### Safety

Participants will be instructed to inform study staff immediately of the occurrence of any adverse events related to study devices (e.g., cutaneous events), or any serious adverse events (SAE) both related and un-related to study devices (e.g., hospitalization, DKA, severe hypoglycemia). Clinical investigators will advise about medical treatment, if necessary. All SAE will be reported to the lead investigator immediately after being reported to research staff or within one day of occurrence.

Technical support will be provided to all participants as needed while using AHCL from study staff and through the device manufacturer’s technical helpline. Any device deficiencies (medical device inadequacies with respect to its identity, quality, durability, reliability, safety or performance, notably including use errors) will be recorded and reported to the device manufacturer. A device deficiency that could have led to a SAE if circumstances had been less fortunate will be managed as a device-related SAE.

### Statistical analysis

Statistical analyses will be performed using the up-to-date version of specialist statistical software (R, SAS, or Stata), and results will be reported in line with the CONSORT statement. The biostatistician will be blinded to intervention assignment and will use non-informative group codes until all analyses are completed. Appropriate descriptive statistics will be presented for all variables, including means and standard deviations for continuous normally distributed variables and counts and percentages for categorical variables. The primary analysis will follow the intention-to-treat principle, with participants analyzed as per randomization allocation. A secondary per-protocol analysis will also be conducted where only those participants in the intervention group using SmartGuard™ for at least 70% of the time will be included. An alpha of 0.05 will be considered statistically significant. Mixed effects regression models will be used to estimate mean differences in outcomes, with 95% confidence intervals and p-values between groups. Models will be adjusted for baseline and stratification variables. A random effect for site will be included. There will be no adjustment for multiple comparisons. Residuals of all models will be plotted to assess whether homoscedasticity assumptions are met. If necessary, outcome variables may be log-transformed or quantile regressions undertaken.

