## Introduction

Maintaining healthy glycemic control is challenging for people with type 1 diabetes (T1D). This is particularly so for children, and adolescents and young adults (henceforth referred to as “youth”) as their attempts to manage glucose levels to target can be limited by risk of hypoglycemia, fear of hypoglycemia, their own or their caregivers’ burden of care, and less treatment adherence e.g. in form of missed bolus insulin delivery and less frequent self-monitoring of blood glucose [1–3]. Accordingly, less than a third of children and youth with T1D achieve glycemic targets known to reduce the risk of developing diabetes complications and improve life expectancy [1, 4]. More efficacious and burden reducing therapies are clearly required to improve outcomes.

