### Sample size

Using a standard deviation of 23 mmol/mol and a within-person correlation of 0.6 [17, 31], a sample size of 64 (32 participants per group) would be required to determine a conservative difference in change in HbA_1c_ of 15 mmol/mol with 90% power to the alpha of 0.05 level (single arm data suggests > 15mmol/mol achievable in this population [17]). To account for 20% loss of data and participant attrition (inflated compared to other trials to allow for potentially greater loss of data due to the high-risk population), a sample size of 80 will be recruited (40 participants per group).

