#### Control arm

Control participants will continue their usual diabetes therapy (MDI or CSII [without automated insulin delivery]) throughout the 13-week RCT, and will receive remote contact from study staff at the same frequencies as described for the intervention group, including insulin dosing and glycemic data reviews, and management interventions as needed. Participants will repeat blinded CGM for continuous collection of end-of-study glycemic data during the final 2 weeks of the RCT. CGM use in the control group will be documented and reported, but no restrictions on CGM use are in place (other than those restricting AHCL/AID).

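### The secondary per-protocol analysis filters only the AHCL arm on SmartGuard use after randomisation, so its between-arm contrast is not protected by randomisation and can be expected to favour AHCL if high users have a better prognosis

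*Protocol article*

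**What the plan says.** The Statistical analysis section of the protocol article makes intention to treat primary: "The primary analysis will follow the intention-to-treat principle, with participants analyzed as per randomization allocation". It then adds: "A secondary per-protocol analysis will also be conducted", with the rule that "only those participants in the intervention group using SmartGuard™ for at least 70% of the time will be included".

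No matching criterion is given for controls. The Control arm section says "Control participants will continue their usual diabetes therapy", meaning injections or a pump without automation, so no SmartGuard percentage can exist for them.

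The same Statistical analysis section specifies mixed models that give between-group mean differences with 95% confidence intervals and p-values. On covariates it says "Models will be adjusted for baseline and stratification variables", plus a random effect for site. The stratification variables, listed under Randomization, are HbA1c band and age band. On testing it says "An alpha of 0.05 will be considered statistically significant", with no multiplicity adjustment.

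Among the factors that limit glucose management in children and youth, the Introduction lists "less treatment adherence e.g. in form of missed bolus insulin delivery and less frequent self-monitoring of blood glucose".

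**The concern.** SmartGuard use is observed after allocation and is partly a matter of behaviour. Under this rule, AHCL participants who engage poorly leave the analysis, while controls who would have engaged just as poorly stay in. The two groups compared are then no longer exchangeable, even though the randomised arms were.

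If engagement also predicts HbA1c whatever the therapy, the contrast mixes the effect of the system with the better prognosis of those who keep using it. Baseline HbA1c carries some information about past engagement but need not capture engagement over the following 13 weeks. The strata are coarse and concern HbA1c and age, not adherence.

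At stake is a secondary estimate that could be read as the effect in people who really use the system, with a p-value whose nominal 5% level may not hold.

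**Working it through.** **1. Residual SD, checked against the plan's own sample size.** The Sample size section gives the inputs: "Using a standard deviation of 23 mmol/mol and a within-person correlation of 0.6", a difference of 15 mmol/mol, 90% power and alpha 0.05 (taken as two-sided). The SD after baseline adjustment is 23 × √(1 − 0.6²) = 23 × 0.8 = 18.4 mmol/mol. Then n per group = 2 × (1.960 + 1.282)² × 18.4² / 15² ≈ 31.6, rounded up to 32. This gives 64 in total, and 64 / 0.80 = 80. The plan's 32, 64 and 80 are reproduced exactly. The raw SD of 23 would give 50 per group and the change-score SD of 20.57 would give 40, so 18.4 is the SD the plan implies.

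**2. Assumptions the article does not supply.**
- p is the share of the AHCL arm reaching 70% SmartGuard use, taken as 60–80%.
- ρ is the correlation between the tendency to use SmartGuard and a better 13-week HbA1c after baseline adjustment, taken as 0.2–0.5. Zero is shown as the reference.

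**3. Expected bias at zero true effect.** Treat adherence as a normal trait, and keep AHCL participants above the cut-off c that retains a share p. The retained mean is then shifted by

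bias = ρ × 18.4 × φ(c) / p,

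where φ is the standard normal density. Results in mmol/mol, all in favour of AHCL:

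| Share kept | φ(c)/p | ρ = 0 | ρ = 0.2 | ρ = 0.3 | ρ = 0.5 |
|---|---|---|---|---|---|
| 80% | 0.350 | 0 | 1.3 | 1.9 | 3.2 |
| 70% | 0.497 | 0 | 1.8 | 2.7 | 4.6 |
| 60% | 0.644 | 0 | 2.4 | 3.6 | 5.9 |

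Example: 70% kept, ρ = 0.3 gives 0.3 × 18.4 × 0.497 = 2.7. Against the design difference, the range is 1.3/15 ≈ 9% to 5.9/15 ≈ 39%.

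**4. Error rate.** The simulation had zero true effect, 40 randomised per arm, regression on arm and baseline HbA1c, only the AHCL arm filtered, and 6,000 runs per setting. Strata and site were not modelled. Two-sided rejection at 0.05 was:

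| Share kept | ρ = 0 | ρ = 0.3 | ρ = 0.5 |
|---|---|---|---|
| 80% | 0.045 | 0.071 | 0.115 |
| 70% | 0.053 | 0.096 | 0.172 |

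When ρ was above zero, nearly all rejections favoured AHCL. With 32 per arm the corresponding rates were lower: 0.063 and 0.099 at 80% kept, and 0.083 and 0.137 at 70% kept.

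**5. Isolating the cause.** Applying the same latent filter to both arms (70% kept, 40 per arm) brought the bias back to about zero and the rejection rate to about 0.052, for ρ of 0.3 and of 0.5. The one-sided filter is therefore what produces the shift. This check is only illustrative, because controls have no SmartGuard measure on which to be filtered.

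**The case against.** The strongest reply is that the direction and size of the bias are assumed. At ρ = 0 there is none. The Introduction's remark concerns missed boluses and infrequent self-monitoring in young people generally and does not mention time in SmartGuard. Use can also fall for device reasons: Platform performance tracks SmartGuard exits and sensor wear, and Safety anticipates skin reactions and device deficiencies. Everyone enrolled has an HbA1c of at least 8.5%, and baseline is in the model, so part of any adherence-related prognosis is already absorbed. All of this stands. A reader might infer that the analysis must favour AHCL, but the documents support only that it is expected to if high users have a better prognosis.

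A second reply is that keeping all controls is an inference, because the article condenses a fuller plan that may contain control criteria. Read literally, the sentence could even exclude controls altogether. But the planned models estimate differences between groups, so keeping controls is the natural reading. Whatever other rule might apply to controls, it could not be a SmartGuard threshold. The one-arm filter is a stated rule, not a missing detail.

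Third, the analysis is secondary, and loss of randomisation is a known limit of per-protocol sets. This stands and bounds the consequence. A reader might infer that the trial's main result is compromised, but the article bases its primary analysis on allocation, and no sample-size or efficacy claim rests on the per-protocol set.

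Finally, an instrumental-variable analysis is not a clean replacement. The Intervention arm section also provides a new pump, a new sensor, training and 72 hours of sensor-augmented pump therapy with predictive low-glucose management. Meal announcement procedures adds a simplified meal method. If these lower HbA1c outside SmartGuard time, the estimator credits SmartGuard with their effect. This objection stands, so such an analysis belongs only as an optional sensitivity analysis.

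**Conclusion.** The point holds in a limited form. As stated, the per-protocol contrast compares an AHCL subset selected after randomisation with controls who cannot be selected in the same way, and it comes with a confidence interval and p-value. It lacks the protection of randomisation whatever the value of ρ, and the planned covariates need not restore it.

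The direction is conditional. The expected error favours AHCL if sustained SmartGuard users would have done better on any therapy, which is plausible but not shown. Its size under the assumed 60–80% retention and ρ of 0.2–0.5 is about 1.3–5.9 mmol/mol at zero true effect. The upper figure needs the least favourable combination of the two assumptions. Only the SD of 18.4 is anchored in the plan's own figures. The intention-to-treat primary analysis is not affected.

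**What to change.** Amend the Statistical analysis wording and any analysis plan that follows it as below:
- Present results for AHCL participants with at least 70% SmartGuard use as descriptive or supportive.
- State beside them that users at this level may differ in prognosis from the rest of their arm and from controls.
- Attach no between-arm p-value and base no efficacy conclusion on this subset.

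Optionally, add a sensitivity analysis on all randomised participants: instrumental-variable (two-stage least squares) regression with baseline adjustment, allocation as the instrument, and the proportion of RCT time in SmartGuard as the exposure, set to zero for controls. State two assumptions with it: that the effect is linear in time used, and that allocation acts on HbA1c only through SmartGuard time. The second is doubtful here because of the new pump, sensor, training and initial sensor-augmented phase. With controls at zero, the estimate is essentially the intention-to-treat effect divided by mean use, so it should not be presented as independent evidence.

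The cost is small. It needs a few sentences of wording and, if the option is taken, one further model on data already being collected. A secondary result loses its formal test, and the optional estimate has a wider interval and its own assumptions.

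### The residual-check fallback can replace the primary HbA1c mean difference in mmol/mol with a ratio or a quantile difference, when unequal variance calls only for a different standard error

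*Protocol article*

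**What the plan says.** The Statistical analysis section of the protocol article sets a default: mixed effects regression giving mean differences between groups, adjusted for baseline and the stratification variables, with a random effect for site. It then adds a check and a remedy. The check is: "Residuals of all models will be plotted to assess whether homoscedasticity assumptions are met". The remedy is: "If necessary, outcome variables may be log-transformed or quantile regressions undertaken". The check covers every model, and neither sentence sets primary HbA1c apart. The same section keeps the biostatistician blinded and working with coded groups until the analyses are finished.

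The Outcome measures section makes the primary outcome HbA1c at the end of the 13-week phase, adjusted for baseline. The Sample size section starts from these inputs: "Using a standard deviation of 23 mmol/mol and a within-person correlation of 0.6". It concludes that 64 participants "would be required to determine a conservative difference in change in HbA_1c_ of 15 mmol/mol with 90% power".

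**The concern.** The only stated diagnostic is unequal variance. Unequal variance does not make a mean difference the wrong quantity to estimate. It means that the usual standard error may be off. Both remedies leave the standard error alone as a problem and change what is estimated. A log model gives a ratio of geometric means, and quantile regression gives a difference in some quantile.

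For secondary outcomes with awkward distributions, that can be sensible. For the primary outcome, the headline result could end up on a scale with no direct link to the 15 mmol/mol on which the trial was sized, because of a feature of the data that did not require it. Readers who want to set the result beside the planned difference, or beside other trials in mmol/mol, would lose the direct comparison.

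**Working it through.** **1. Which effect measure does the sample size belong to?**

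Inputs from the Sample size section: SD 23 mmol/mol, within-person correlation 0.6, difference 15 mmol/mol, power 90%, alpha 0.05 (taken as two-sided, since one-sided gives 26 per group), loss 20%.

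Formula: n per group = 2 × (1.960 + 1.282)² × SD² / 15².

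- Baseline-adjusted mean difference: SD = 23 × √(1 − 0.6²) = 18.4, so n = 31.6, rounded up to 32. The total is 64, and 64 / 0.80 = 80. Both stated figures reproduce.
- Change score: SD = 23 × √(2 × 0.4) = 20.57, so n = 40 per group. This does not reproduce.
- Unadjusted 13-week value: SD = 23, so n = 50 per group. This does not reproduce.

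The plan's figures are therefore those of a baseline-adjusted mean difference. Its power at 32 per group is 90.3% (normal approximation) or 89.4% (t distribution).

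**2. What does 15 mmol/mol become on the log scale?**

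The ratio is 1 − 15 / control mean. The control mean at 13 weeks is not given. I take 70 to 130 mmol/mol, which spans the entry threshold (69) to the point-of-care upper limit (130).

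| Assumed control mean (mmol/mol) | Ratio equal to a fall of 15 |
|---|---|
| 70 | 0.786 |
| 90 | 0.833 |
| 100 | 0.850 |
| 130 | 0.885 |

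Read the other way, a constant ratio of 0.85 is a fall of 0.15 × 70 = 10.5 at one end and 0.15 × 130 = 19.5 at the other. One log-scale effect does not correspond to one difference in mmol/mol.

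**3. Does unequal variance damage the planned test?**

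With n per arm equal, the pooled variance is the average of the two arm variances. The pooled squared standard error, 2 × [(s₁² + s₂²)/2] / n, therefore equals the unpooled one, (s₁² + s₂²) / n. For example, with SDs of 18.4 and 9.2 and 32 per arm, both are (338.56 + 84.64) / 32 = 13.2, a standard error of 3.64.

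Simulation agrees. ANCOVA at 32 per arm, no true effect, normal errors, and AHCL residual SD at 100%, 67% and 50% of control gave type I error of 4.8%, 5.2% and 5.0% (20,000 runs each). A separate run of the same scenarios gave 4.6% to 5.1%.

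Unequal retention would weaken this protection. Suppose 28 control and 36 AHCL participants remain, with SDs 18.4 and 9.2.

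- Pooled variance: (27 × 338.56 + 35 × 84.64) / 62 = 195.2.
- Pooled standard error: √[195.2 × (1/28 + 1/36)] = 3.52.
- Unpooled standard error: √(338.56/28 + 84.64/36) = 3.80.

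The usual error would be about 7% too small. A robust or arm-specific variance corrects that without changing the effect measure.

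**The case against.** The strongest reply is that the default is fixed and the fallback is named in advance, tied to residuals, and conventional. The threshold for acting, the quantile and the order of the options are details that an article may leave to an analysis plan, and one may exist. That stands, and the absence of a numerical criterion is not the complaint here. What remains is a remedy that the article itself states, that covers the primary outcome, and that does not match its trigger.

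The blinding is a real safeguard and also stands. It limits choosing a model by the direction of effect. Coded groups still show the size of a difference, and blinding does not keep the effect measure from changing.

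Two stronger readings are tempting, and the document supports neither.

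- **Inflated type I error.** A reader might see three candidate models sharing one alpha. Taking the best of the three p-values gave about 7% in simulation, against about 5% for the planned model, but the text ties the choice to residuals and not to p-values. When a Breusch-Pagan test at 0.05 triggered the log model, the error was 4.9%, against 4.8% for the fixed model (4,000 runs, one assumed scenario, log option only).
- **Lost power.** Under normal errors, median regression multiplies the SD by √(π/2), to 23.06. Power falls from 89.4% to 72.6% at 32 per group, or from 95.0% to 81.9% at the 40 recruited. But normal errors are where the fallback is less likely to be invoked. In a simulation with skewed errors, the log model had more power than the mean model (92.8% against 87.2%). These figures are not the cost of the rule as written.

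Nor does the document give any figure showing that unequal variance will occur in HbA1c. That AHCL may compress high values is plausible but conjectural.

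**Conclusion.** The point holds in a limited form. As written, the plan lets a residual plot move primary HbA1c from a baseline-adjusted mean difference in mmol/mol to a ratio or a quantile difference. The harm is to interpretation and to the link with the powered contrast. It does not extend to the validity of the test or to the sample size: 64 and 80 are correct for the adjusted mean difference.

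The size of the mismatch is shown by the ratio range of 0.79 to 0.88, which rests on assumed control means. The claim that unequal variance matters little rests on equal arms and, in the simulation, on normal errors; it weakens if retention differs between arms. If an unseen analysis plan already keeps HbA1c on the mmol/mol scale, only the article's wording needs aligning.

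**What to change.** State that the primary result is the baseline-adjusted mean difference in 13-week HbA1c, in mmol/mol, whatever the residuals show. If the residuals show unequal variance, use robust standard errors (for example HC3) or arm-specific residual variances. Report log or quantile models for HbA1c only as labelled sensitivity analyses.

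The fallback may stay for skewed secondary outcomes. Where exact zeros occur, as they may for time below 54 mg/dL (Glycemic metrics section), a logarithm is undefined; name a quantile or fractional-response model for those outcomes in advance.

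The cost is wording, and possibly a slightly wider interval for the primary estimate. The sample size does not change.

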## Discussion

Despite ongoing iterative advances in diabetes management, children, adolescents and young adults with T1D remain at high risk for out-of-target glycemia [4, 50–52]. This results in greater experience of both acute and chronic diabetes complications, as well as an increased likelihood of experiencing considerable diabetes- and non-diabetes-related burdens, including diabetes distress, stigma, psychiatric morbidity, and family/inter-personal conflict [53, 54]. AHCL, already the gold standard therapy for people with healthier glycemia [55–57], remains under-utilized in those with out-of-target control, which may in fact be used as a reason for exclusion from technology use, both clinically and in all randomized trials to date [9–14]. Our hypothesis is that for children and youth not meeting internationally recommended glycemic targets, AHCL should be the gold standard therapy and is likely to provide benefits for most with regards to burden reduction, psychosocial wellbeing, and glycemia. To our knowledge, the CO-PILOT trial is the first RCT to elucidate the impact of AHCL among this largely technology naïve, high-risk child and youth population (particularly those with HbA_1c_ > 10% [86 mmol/mol]) compared with traditional therapies.

Important strengths of the CO-PILOT trial are the outpatient structured training approach with intentional recruitment of a child and youth population with: (1) elevated HbA_1c_ ≥ 8.5% (≥ 69 mmol/mol); (2) diverse ethnic and socioeconomic backgrounds; (3) current MDI and CSII use without AID exposure; (4) opportunity for rapid outpatient on-boarding to automation with simplified carbohydrate counting options to avoid traditional potential delays around training location and carbohydrate counting education. Other strengths are the study duration with the continuation phase providing access to all participants out to week 54 as well as the in-depth psychosocial assessments (including sleep quality and qualitative work) to provide a greater understanding of AHCL acceptability and benefit. Limitations of the study include complexities of the utilized blinded CGM system which tends to lose data above 400 mg/dL (22.2 mmol/L) and which if anything leads to under-estimation of time above range at baseline and in the control group, but does not impact the HbA_1c_ primary outcome. Real-world clinic support may also differ from what is provided during the study, however, all efforts have been made to ensure translatable management including comparable contact with control participants, outpatient-based training and management, as well use of telehealth/phone-based remote contact.

In conclusion, in the CO-PILOT trial we aim to show that AHCL will have both immediate and long-term health benefits for participants and, where applicable, their caregivers. These results have the potential to translate into global impact by providing gold standard RCT evidence establishing the effectiveness and safety of AHCL in children and youth struggling with diabetes management and burden. This evidence is essential if we are to establish AHCL as the gold standard for glucose lowering therapy in people with T1D regardless of pre-conceptions related to their prior glucose control.
